**Table 1 Tab1:** **Serodiscordant couples sample size calculations**

Percentage of HIV men who are on ART and have undetectable BPVL	Reduction in HIV incidence in HIV-negative men with partners with undetectable BPVL	Required number of HIV seroconversion events	Total sample size required
**60%**	0.75	18	631
	0.85	11	436
	0.95	7	305
**70%**	0.75	15	624
	0.85	9	413
	0.95	5	272
**80%**	0.75	14	692
	0.85	7	429
	0.95	4	256
**90%**	0.75	17	1008
	0.85	7	563
	0.95	3	276

### Eligibility

Homosexual men in sexual partnerships meeting the following criteria are eligible to enroll in the study: (1) Both partners aged 18 years or over; (2) One partner is HIV-positive and the other partner HIV-negative at baseline; (3) Partners must have anal sex with each other at least once per month on average; (4) Partners must believe they will still be having anal sex with each other by the time of the HIV-positive partner’s next viral load test (that is, between three to six months after baseline); and (5) Both partners must agree to attend clinic visits at least twice per year. HIV-positive partners can enroll in the study irrespective of whether they are taking ART or not, or whether their BPVL is undetectable or detectable. Couples can enroll irrespective of whether they engage in unprotected or protected anal intercourse with each other.

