**Methods/Design:**

The *Opposites Attract Study* is an observational prospective longitudinal cohort study of male homosexual serodiscordant partnerships running from 2012 to 2015 and conducted in clinics throughout Australia, Brazil and Thailand. Couples attend two or more clinic visits per year. The HIV-positive partner’s viral load is tested and the HIV-negative partner is tested for HIV antibodies at every clinic visit. Results from any tests for sexually transmitted infections are also collected. Detailed behavioural questionnaires are completed by both partners at the time of each visit. The primary research question is whether HIV incidence is lower in those couples where the HIV-positive partner is receiving HIV treatment compared to couples where he is not receiving treatment. A voluntary semen sub-study will examine semen plasma viral load in a subsample of HIV-positive partners in Sydney, Rio de Janeiro and Bangkok. In cases of seroconversion of the initially HIV-negative partner, phylogenetic analysis will be conducted at the end of the study on virus from stored blood samples from both partners to determine if the infection came from the HIV-positive study partner. Men in new serodiscordant relationships will specifically be targeted for recruitment.

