### Enrolment and clinic visits

In Australia, couples are enrolled at the clinic the HIV-positive partner attends for routine clinical management. In Brazil and Thailand, couples are enrolled at the study clinic. The study is clearly explained, and consent forms signed. Participants must sign the consent forms while their partner is outside the room, to minimise the risk of coerced participation. Both partners complete an HIV transmission knowledge quiz and education process to ensure they understand how HIV is transmitted in the context of serodiscordant male-to-male sex. They are encouraged to read the *Opposites Attract* HIV transmission factsheet before attending the enrolment visit.

Once enrolled, both partners undergo a baseline clinic visit, involving pathology samples testing (viral load, CD4, HIV antibodies, STIs) and the collection of biological samples for storage. Follow-up visits occur each time regular viral load monitoring of the HIV-positive partner occurs, a minimum of two times per year. Partners do not need to attend their clinic visits at the same time. However, they must attend within two weeks of each other.

Table 
2 indicates all procedures associated with each clinic visit. A viral load test is required for an HIV-positive partner’s visit to be considered a study visit, while an HIV antibody test is required for an HIV-negative partner’s visit to be considered a study visit. In Australia, STI tests are conducted as indicated by Australian guidelines

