### HIV seroconversion of initially HIV-negative partners

In cases of HIV seroconversion among initially HIV-negative participants, each clinic will follow its standard approach, typically including immediate referral to an HIV specialist for further testing and monitoring, referral to professional and peer-based support services, and discussion of treatment options. The study protocol does not mandate any specific approach to how clinics should deal with HIV seroconversion.

At the end of the study, phylogenetic analysis will be conducted on paired stored blood samples from both partners. Epidemiological relationships will be established by analyses of *env* and *gag-pol* sequences derived from plasma as well as PBMC from these blood samples. Sequence alignment will be performed by using either Clustal X or MUSCLE software. Phylogenetic analyses including patient derived sequences and background sequences derived from the Los Alamos database will assess linkage between different viruses by inferred maximum likelihood phylogeny, neighbour joining methods, pairwise distances, Bayesian inference and bootstrap analyses
[16]. Tree visualisation will be performed using, for example, TreeView or UGENE software.

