### Data analysis

The primary analyses aim to determine if HIV incidence is reduced in the HIV-negative partner when the HIV-positive partner: (1) is taking ART compared to not taking ART, and (2) has undetectable viral load compared to detectable viral load. These incidence rates will be calculated by dividing the number of phylogenetically linked seroconversions for each group by the total number of person-years of follow-up for that group. If there are no phylogenetically linked seroconversions, the upper limit of the confidence interval around a transmission rate of zero will be determined. Given that laboratories utilise different assays for viral load testing which have various lower limits of detection (e.g. 20, 40, 50, or 150 copies per mL), the precise definition of ‘undetectable’ and ‘detectable’ BPVL differs across sites. This will be taken into account in analysis, and a standardised cut-off may be used for directly measured BPVL (e.g. less than 400 copies per mL).

Two of the study questions relate to SPVL. First, in the subsample of couples included in the Semen Sub-Study, HIV incidence will be compared between couples with detectable versus undetectable SPVL in the HIV-positive partner. Second, within the HIV-positive partners participating in the Semen Sub-Study, BPVL and SPVL will be compared at each study visit. HIV RNA levels in seminal plasma will be determined using an adaptation of an in-house assay for separation of seminal plasma from human samples and the COBAS® AmpliPrep/COBAS® TaqMan® system.

The behavioural and attitudinal data collected from the participant questionnaires will allow for both cross-sectional and longitudinal analyses. A key focus will be on the question of whether gay men in serodiscordant relationships use condoms less often when the HIV-positive partner has undetectable viral load
[17]. This will be explored both through directly measured and perceived viral load, both categorically in terms of those who have/do not have UAI as well as by the number and type (insertive/receptive and with/without ejaculation) of acts of UAI, and in relation to attitudes regarding TasP, communication within relationships, and relationship agreements about viral load and sexual practice.

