## Discussion

While there is strong evidence for the effectiveness of ART to substantially reduce the risk of HIV transmission in heterosexual serodiscordant couples, there is very limited published evidence on TasP within homosexual male serodiscordant couples or in relation to anal intercourse. *Opposites Attract* and the *PARTNER Study*
[7] appear to be the only two clinical studies exploring these questions. The *PARTNER Study* focuses on measuring the HIV incidence in both heterosexual and homosexual serodiscordant couples having unprotected anal and/or vaginal intercourse, and is restricted to couples where the HIV-positive partner is receiving ART at baseline. By contrast, *Opposites Attract* will allow the calculation of HIV incidence in couples where HIV-positive partners are on ART or not on ART, and with undetectable versus detectable BPVL (and SPVL in a subsample of couples). Furthermore, the detailed behavioural and attitudinal data from the participant questionnaires will allow exploration of many contextual factors associated with HIV risk, condom use and the negotiation of sexual practice within couples.

Measuring the effect of ART on transmission is impacted by whether serodiscordant couples have unprotected intercourse with each other. In *Opposites Attract*, the decision was made not to restrict enrolment to those couples reporting UAI with each other in the months before baseline (as in the *PARTNER Study*). This was because in a pilot study we conducted in Melbourne, it was found that participants were wary of enrolling or expressing interest in the study if they were required to report having UAI with each other to their clinician. Thus, the eligibility criterion for the main study was changed to the couples having anal intercourse (protected or unprotected) with each other at least once per month on average. The level of risk within the cohort will be monitored over time and changes may be made to this criterion in the future if necessary.

Furthermore, in preparation for *Opposites Attract*, we analysed cohort data of HIV-negative men in Sydney and found that amongst HIV-negative who reported being in a serodiscordant relationship of one year or less, the HIV incidence was approximately 6 per 100 person-years as compared to much lower incidence in those who reported longer relationships, suggesting that the riskiest period for HIV-negative men in serodiscordant relationships is the first year of the relationship

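### A linked infection acquired from the study partner just before enrolment can be counted as an on-study transmission, because baseline status rests on an antibody test and linkage does not date infection

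*Protocol article*

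**What the plan says.** The serostatus criterion (Eligibility) is that "One partner is HIV-positive and the other partner HIV-negative at baseline". It names no assay and no window rule.

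The baseline visit consists of "pathology samples testing (viral load, CD4, HIV antibodies, STIs) and the collection of biological samples for storage" (Enrolment and clinic visits). Table 2, which is said to cover all visit procedures, assigns these by partner. Viral load belongs to the positive partner. The negative partner has an antibody test, STI tests and stored samples. The same section adds that "an HIV antibody test is required for an HIV-negative partner’s visit to be considered a study visit", and the Abstract that "the HIV-negative partner is tested for HIV antibodies at every clinic visit".

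The primary rates are obtained by "dividing the number of phylogenetically linked seroconversions for each group by the total number of person-years of follow-up for that group" (Data analysis). The groups are on versus off ART, and undetectable versus detectable blood plasma viral load (BPVL). On linkage: "At the end of the study, phylogenetic analysis will be conducted on paired stored blood samples from both partners" (HIV seroconversion of initially HIV-negative partners). The article gives no rule for dating an infection or for setting aside one already present at enrolment.

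On recruitment, the Abstract says: "Men in new serodiscordant relationships will specifically be targeted for recruitment". The Discussion gives the reason, for men whose relationship had lasted up to a year: "the HIV incidence was approximately 6 per 100 person-years as compared to much lower incidence in those who reported longer relationships".

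Plasma, serum and buffy coat are stored from both partners at baseline (Summary of study design; Table 2). The stated uses of stored blood are phylogenetics and, possibly, genetic resistance factors.

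**The concern.** Suppose a man is infected by his study partner in the weeks before enrolment. He can be antibody-negative at baseline and antibody-positive at the next visit. His virus will be linked to his partner's, so he meets the definition of a primary event although nothing was transmitted during follow-up. The design makes exposure around enrolment likely: couples must have anal sex at least monthly, condom use is not required, and recruitment seeks out the relationship phase with the highest incidence.

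Two errors follow. First, the event enters the numerator while the exposure time that produced it lies outside the denominator, so the rate in that group is too high. Second, if the positive partner started ART or became suppressed around enrolment, the event is charged to a status he did not have at transmission. In the undetectable group this could look like transmission under suppression. In the detectable or untreated group an extra event makes the apparent benefit too large.

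**Working it through.** **1. Reproduce the plan's zero-event limits.** Inputs (Sample size): 640 couple-years, 80% or 90% undetectable, one-sided 97.5%. Exact Poisson upper limit for x events in T years: U = χ²(0.975; 2x+2) / (2T).
- 80%: T = 640 × 0.80 = 512. For x = 0, U = 3.689/512 = 0.72 per 100 person-years.
- 90%: T = 640 × 0.90 = 576. For x = 0, U = 3.689/576 = 0.64.

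Both match the article.

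**2. Add one pre-enrolment event to the undetectable group.** For x = 1 the numerator is 5.572.
- T = 512: 5.572/512 = 1.09.
- T = 576: 5.572/576 = 0.97.

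Each limit rises by about 51% (5.572/3.689 = 1.51).

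**3. Effect on the comparative scenario.** Inputs: 60% undetectable, 631 couple-years, 5.0 per 100 person-years if detectable, 75% reduction.
- Detectable: 631 × 0.40 = 252.4 years, × 0.05 = 12.62 events.
- Undetectable: 631 × 0.60 = 378.6 years, × 0.0125 = 4.73 events. Rate ratio 0.25.
- One extra undetectable event: (5.73/378.6)/0.05 = 0.30.
- One extra detectable event instead: 0.0125/(13.62/252.4) = 0.23.

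The shift is modest and can go either way.

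**4. Expected window infections from all sources.** Formula: couples × incidence × window/52. The incidence is the article's 6 per 100 person-years. The window (3 to 6 weeks) and the number of new couples (150 or 300) are assumptions; the article gives neither.
- Per man: 0.06 × 3/52 = 0.35%; 0.06 × 6/52 = 0.69%.
- 150 new couples: 0.5 to 1.0.
- 300 new couples: 1.0 to 2.1.

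Wider assumptions (150 to 350 couples, 2 to 12 weeks) give 0.35 to 4.85 at 6 per 100 person-years, and 0.13 to 1.78 at the overall 2.2 per 100.

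The 6 per 100 is neither restricted to linked infections nor split by viral load. If, for illustration, half were linked, 150 couples give 0.26 to 0.52 and 300 give 0.52 to 1.04.

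**5. Expected number misassigned to the undetectable group.** This needs a positive partner who was detectable at transmission and undetectable afterwards. Assume 300 couples, 5 to 20% switching within the window (15 to 60 couples), the article's 5.0 per 100 person-years for detectable partners, and every infection linked.
- Low: 15 × 0.05 × 3/52 = 0.04.
- High: 60 × 0.05 × 6/52 = 0.35.

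As a harsher check, scale the first-year rate by the article's own ratio of detectable to overall incidence: 6 × 5.0/2.2 = 13.6 per 100 person-years. The range becomes 15 × 0.136 × 3/52 = 0.12 to 60 × 0.136 × 6/52 = 0.94, still below one.

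**The case against.** The endpoint is not antibody conversion alone. It also requires linkage, so window infections from outside the couple never reach the numerator. This stands, and it limits the problem to infections from the study partner.

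A reader might infer that every such event falls in the wrong ART or viral-load group. The documents do not support that. With a window of weeks, a partner detectable throughout puts the event in the right group. If he was suppressed throughout, it really was transmission under suppression, with only its timing wrong. Misassignment needs a change of status around enrolment. The recorded ART regimen, the treatment questions and the viral load at every visit would help to recognise one.

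A spurious event in the undetectable group also works against the study's hypothesis, so it cannot give false reassurance about suppression. This is true for that group, but an extra event in the detectable group pushes the comparison the other way (step 3).

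The strongest objection is that a condensed article may leave the handling of seroconverters to a fuller document, and that nothing in it prevents a later test of stored plasma. That is fair as regards whether an operational rule exists. It does not dispose of the point: the article itself fixes the test for the negative partner and the numerator, and under those two statements a pre-enrolment linked infection counts as an event.

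**Conclusion.** The point holds in limited form. As written, a linked infection acquired just before enrolment can enter the primary numerator without its at-risk time. It carries the wrong exposure status only if the positive partner's status changed around enrolment.

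The expected number is about 0.5 to 2 from all sources, fewer linked, and probably below one misassigned to the undetectable group. These figures rest on an assumed window, number of couples and switching share, none of which is in the article. The move from 0.72 to 1.09 (or 0.64 to 0.97) describes what happens if one such event occurs; it is not a forecast that it will. The planned limits themselves are correct.

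It would be too strong to conclude that the design is unsound or that transmissions will be misattributed. What justifies acting is that a zero-event result can be overturned by one man, and the sample needed to classify him is already stored.

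**What to change.** Add a rule to the analysis section. At study end, test the stored baseline plasma of each phylogenetically linked seroconverter for HIV RNA, at minimum those first antibody-positive at their first follow-up visit. Classify RNA-positive men as infected at baseline and exclude them from both numerator and denominator of the primary incidence analyses. List them separately with the positive partner's ART and viral-load history around enrolment, so that a possible transmission under suppression is not lost from view. Report the primary rates with and without them. If a fuller protocol already contains such a rule, cite it in the analysis section.

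The cost is one assay per linked seroconverter on a sample already held (about 18 or fewer in the primary power scenario) and a few lines of text. No new visit or sample is needed. The downside is possibly one or two fewer countable events.

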### Clinical sites

As of September 2014, fourteen high HIV caseload public (n=6) and private (n=8) clinics in Australia are participating in the study, along with one clinic in Rio de Janeiro, Brazil, and another clinic in Bangkok, Thailand. New sites may be initiated at a later time.

### Recruitment

Clinics are free to employ a range of recruitment strategies to identify and recruit potential participants, depending on what is deemed appropriate for each clinic. Mostly, couples are recruited when clinicians raise the study directly with HIV-positive patients or HIV-negative patients known to have an HIV-positive regular partner. Interested patients are given information about the study and are asked to speak to their regular partner about participation. They are contacted by the clinic-based study coordinator and an enrolment visit is arranged if the couple is both interested and eligible. Community-based study promotion is also implemented in the form of print and online advertising, attendance and/or presentations at community events, and engagement with community-based partner organisations.

### Enrolment and clinic visits

In Australia, couples are enrolled at the clinic the HIV-positive partner attends for routine clinical management. In Brazil and Thailand, couples are enrolled at the study clinic. The study is clearly explained, and consent forms signed. Participants must sign the consent forms while their partner is outside the room, to minimise the risk of coerced participation. Both partners complete an HIV transmission knowledge quiz and education process to ensure they understand how HIV is transmitted in the context of serodiscordant male-to-male sex. They are encouraged to read the *Opposites Attract* HIV transmission factsheet before attending the enrolment visit.

Once enrolled, both partners undergo a baseline clinic visit, involving pathology samples testing (viral load, CD4, HIV antibodies, STIs) and the collection of biological samples for storage. Follow-up visits occur each time regular viral load monitoring of the HIV-positive partner occurs, a minimum of two times per year. Partners do not need to attend their clinic visits at the same time. However, they must attend within two weeks of each other.

Table 
2 indicates all procedures associated with each clinic visit. A viral load test is required for an HIV-positive partner’s visit to be considered a study visit, while an HIV antibody test is required for an HIV-negative partner’s visit to be considered a study visit. In Australia, STI tests are conducted as indicated by Australian guidelines
[15]. In Brazil and Thailand, syphilis, gonorrhoea and chlamydia tests are conducted at every study visit. At certain visits, extra blood samples are taken for storage from both partners, and an extra anal swab taken from HIV-negative partners. These samples are processed and stored at local laboratories and shipped to the central laboratory in batches. The blood samples allow for later phylogenetic testing of the partners’ virus in cases of seroconversion of the initially HIV-negative partner. In addition, the specimens may potentially be used to identify genetic factors associated with resistance to HIV acquisition in HIV-negative partners. The anal swabs are taken to later test for rectal herpes simplex virus (HSV) and human papillomavirus (HPV). In Sydney, Rio de Janeiro and Bangkok, HIV-positive participants can elect to join the Semen Sub-Study whereby they provide a semen sample at the time of each clinic visit. The semen samples are processed and stored for later viral load and phylogenetic testing.

**Table 2 Tab2:** **Procedures associated with each clinic visit**

	Baseline visit	First visit of calendar year	All other follow-up visits	Seroconversion visit ^1^
**HIV-Positive partner**				
Viral load test	X	X	X	X
CD4 Count	X	X	X	X
STI tests^3^	X	X	X	X
Blood samples for storage	X	X		X
Semen sample *(optional)* ^2^	X	X	X	X
**HIV-Negative partner**				
HIV antibody test	X	X	X	X
STI tests^3^	X	X	X	X
Blood samples for storage	X			X
Anal swab for storage	X			X

^1^Seroconversion visits only occur if the HIV-negative partner seroconverts during follow-up.

^2^The semen sub-study is only available at certain sites.

^3^At Australian clinical sites, STI tests are conducted as indicated. In Brazil and Thailand, they are conducted at every visit.

### Data collection

Data are collected via electronic case record forms (eCRFs) completed by clinic staff and online computer-assisted self-interview from both HIV-positive partners and HIV-negative partners. The eCRFs include: enrolment information, clinic visit information (including the HIV-positive partner’s ART regimen), and pathology results information. For HIV-positive partners participating in the Semen Sub-Study, further information is entered upon receipt of the sample. Participants are asked to complete their questionnaires at the clinic visit, or within 48 hours of the visit. As the questionnaires are online, they can be accessed by participants in their homes. Clinicians and clinic staff do not have access to the behavioural questionnaire information regarding their patients, and participants are explicitly informed of this. Table 
3 indicates the content categories of the HIV-positive partner and HIV-negative partner questionnaires. Baseline and follow-up questionnaires are very similar. Finally, all initially HIV-negative partners who acquire HIV during follow-up will be invited to participate in a qualitative interview regarding their seroconversion. Further qualitative interviews with other study participants may also be conducted as part of a sub-study.

